|-----------------------------|---------------------------------------------------------------------------------------------------------------------------------------------------------------------------------------------------------------------------------------------------------------------------------------------------------------------------------------------------------------------------------------------------------------------------------------------------------------------------------------------------------------------|
|                             | Experimental care (5 patients): standard clinical care with cervical cooling and systemic cooling allowed as a rescue procedure if temperature targets not achieved;                                                                                                                                                                                                                                                                                                                                         |
| Planned Study Period | 90 days – the trial will be interrupted early if there is any concern regarding the safety of the device.                                                                                                                                                                                                                                                                                                                                                                                                           |
| Primary Objective    | 
Safety. Describe number and severity of complications associated with induction and of hypothermia using selective cervical cooling:
 
 
• failure to maintain the brain within target temperature;
 
• number of instances where external cooling blankets or ice-cold saline had to be used as a rescue strategy to achieve target temperature;
 
• duration and severity of cerebral hyperthermia;
 
• any other adverse event;
 
 |

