## 2. OBJECTIVES

### 2.1 Primary Objective

**Safety.** Describe number and severity of complications associated with induction and maintenance of hypothermia using selective cervical cooling:

- failure to maintain the brain within target temperature;
- number of instances where external cooling blankets or ice-cold saline had to be used as a rescue strategy to achieve target temperature;
- duration and severity of cerebral hyperthermia;
- any other adverse event;

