### 2.2 Secondary Objectives

**Proof of concept.** Describe the ability of the device to deliver selective brain cooling, and its effectiveness:

- differential brain-to-core temperature as evidence of selective cooling (between-group comparison);
- brain temperature within target parameters (between-group comparison);

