#### 6.3 Analysis of Endpoints

Descriptive statistics will be used to report demographics and rate and nature of adverse events.

Non parametric tests will be used for between-group comparison of temperature data and paired data non parametric statistic tests for the brain/body differential temperature analysis.

Further exploratory data analysis of association between brain physiology, brain temperature, brain-body temperature gradients will be performed in the two groups to generate hypotheses for a larger clinical trial.

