## 7. ETHICAL AND REGULATORY COMPLIANCE

The main ethical challenge is around the issue of consent in comatose patients. Our group has extensive experience on the matter. Whenever possible, a “consultee” is identified and their opinion sought about the potential participant’s wishes and feelings in relation to the project, and whether he or she would have wanted to take part in the study. A member of the research team will approach the consultee to explain the study and its implications. Subjects are free to withdraw, or be withdrawn by their consultee if appropriate, at any point in the study, and they need not state a reason.

In regards to randomization, patients randomized to selective brain cooling using the Neuronguard prototype will be closely monitored and whenever target temperature cannot be achieved (or if there is any deterioration in brain physiology) the treating clinical will resort to systemic cooling, either by rapid infusion of ice cold saline or surface body cooling.

Participants in study group face the risk of lesions on the skin of the neck where cooling is applied. In order to minimize this risk we have created a controlled cooling system that senses the temperature of skin and adjust the heat extraction according to a pre-set level considered safe. The skin of the neck is checked by the research nurse each time the brain and core temperature are measured. In case any sign of lesion is present the treatment is immediately stopped.

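### The between-group temperature endpoints are worded as the device's own effect, but as written the in-target comparison measures the device plus systemic rescue

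*Protocol*

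**What the plan says.** The aim in section 2.2 is to "Describe the ability of the device to deliver selective brain cooling, and its effectiveness". Two measures serve it: "differential brain-to-core temperature as evidence of selective cooling (between-group comparison") and "brain temperature within target parameters (between-group comparison"). The Study Design row of the Synopsis goes further and calls both primary outcomes, whereas the objectives list them as secondary.

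The Planned Sample Size row of the Synopsis describes the experimental arm as cervical cooling with "systemic cooling allowed as a rescue procedure if temperature targets not achieved". Section 7 widens the trigger: "whenever target temperature cannot be achieved (or if there is any deterioration in brain physiology) the treating clinical will resort to systemic cooling". The systemic methods named there, ice-cold saline and surface cooling, are those that section 3 specifies for Group 1.

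Section 3 fixes 48 hours of monitoring regardless of targets, with each target recorded as a value ±0.5 °C. Section 6.3 says "Non parametric tests will be used for between-group comparison of temperature data" and adds paired non-parametric tests for the brain/body differential. It has no rule for temperatures recorded after rescue has begun.

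Section 2.1 lists, under the primary safety objective, failure to hold target, the duration and severity of cerebral hyperthermia, and "number of instances where external cooling blankets or ice-cold saline had to be used as a rescue strategy to achieve target temperature".

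**The concern.** A missed target triggers rescue, and rescue then acts on the very temperature being analysed. The rescue treatment is also the control treatment. The less well the device holds target, the more of Group 2's 48 hours is spent on what Group 1 receives. If all those hours enter the in-target comparison, its result describes a strategy of device first and systemic cooling when needed. That is a legitimate quantity, but it is not the one that section 2.2 names.

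The Synopsis makes a larger study conditional on the device showing that it can cool the brain selectively. With five device patients, one or two who spend most of the window on systemic cooling can change the reading. Section 2.1 asks for the number of rescues, and section 3 provides for an hourly chart of temperature targets. Nothing in the protocol calls for rescue start and stop times. If they are not captured, no later analysis plan can reliably separate device time from rescued time.

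**Working it through.** The protocol gives no effect size, test level, power or expected time in target, so there is no stated figure to reproduce. What follows illustrates size only.

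**From the protocol:** 5 patients per arm; 48 hours of monitoring; rescue permitted on a missed target; non-parametric tests.

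**Assumed:** the in-target shares, rescue delays and restoration rates below, a two-sided exact Mann-Whitney test, and a 0.05 level.

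**1. Device that works part of the time.** Let p be the share of hours the device alone holds target, and r the share of the remaining hours that rescue restores. Observed share = p + (1 − p)r.

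| p | r = 0.80 | r = 0.90 |
|---|---|---|
| 0.30 | 0.30 + 0.70 × 0.80 = 0.86 | 0.93 |
| 0.50 | 0.50 + 0.50 × 0.80 = 0.90 | 0.95 |
| 0.70 | 0.70 + 0.30 × 0.80 = 0.94 | 0.97 |

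This formula has no explicit delay before rescue and no carry-over after it.

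**2. Device with no effect, with delay.** The patient is out of target until rescue at d hours, then in target for the standard-care share q. Observed share = q(48 − d)/48. For q = 0.90 and d = 1: 0.90 × 47/48 = 0.88.

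| d (hours) | q = 0.80 | q = 0.90 | q = 0.95 |
|---|---|---|---|
| 1 | 0.78 | 0.88 | 0.93 |
| 2 | 0.77 | 0.86 | 0.91 |
| 4 | 0.73 | 0.83 | 0.87 |
| 8 | 0.67 | 0.75 | 0.79 |

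If time from rescue is not credited to the device, the share is 0 in every cell.

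**3. What a 5 v 5 test would see.** In-target shares were drawn from Beta(18, 2), mean 0.90, with the device arm's multiplied by (48 − d)/48, in 4,000 simulated trials per delay. The chance of p < 0.05 on observed data is 5%, 11%, 34% and 79% for rescue at 1, 2, 4 and 8 hours. With rescued time scored as not achieved, the arms separate completely. The p-value is then 2/252 = 0.008 and the chance is 100%.

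**4. Brain-to-core difference.** Let f be the rescued fraction of hours, gD the gradient on the device and gS that under standard care. If rescued hours show gS, the Group 2 mean is (1 − f)gD + f·gS, and its difference from Group 1 is (1 − f)(gD − gS). Half the hours rescued would halve the contrast. This is dilution towards standard care and does not create apparent selectivity. The assumption that rescued hours show gS is a simplification, because the protocol does not say whether cervical cooling continues during rescue.

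**5. Do the primary items show the failure?** A rescue lasting 40 hours and one lasting 1 hour each count once. Failure to hold target, if measured as time, and the duration of hyperthermia are both shortened when rescue works. Of the temperature-related items, only the rescue count is not improved by rescue, and it has no duration.

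**The case against.** A reader might infer that the protocol analyses rescued temperatures as the device's own achievement. It does not say so. Section 6.3 is silent on rescued data, does not say that all hours are pooled, and does not mention time in target. A statistical analysis plan that is not shown could set the rule. This stands, and the point must be confined to what the protocol fixes: an objective worded as the device's effect, paired with a comparison that does not isolate it. An analysis plan could supply the rule, but could not reliably recover rescue times that were never recorded.

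A reader might also infer that a failing device could pass through the whole trial unnoticed. Section 2.1 contradicts that, because rescues and failure to hold target are primary safety items. The masking concerns the in-target comparison, and the safety items offset it in part.

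Three further objections stand. The figures above rest on assumed inputs, and late rescue would expose the device. Dilution of the gradient probably works against the device, so a false positive on selectivity is unlikely by this route. In a pilot with no formal sample size calculation, test level or margin, nothing says that a non-significant result will be read as equivalence.

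The obvious remedies also have limits. Restricting the gradient to hours on cervical cooling alone selects hours and patients by how well the device did. Section 7 permits rescue for deteriorating brain physiology, which may occur while target is held, so counting every rescued hour as a failure would be unfair. Cold saline also has effects that outlast the infusion, so a stop time does not cleanly end its influence.

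**Conclusion.** The point holds as a mismatch between objective and comparison. As written, the in-target comparison estimates device plus rescue, while section 2.2 words it as the device's effectiveness. Under an assumed 90% in-target share for standard care, a device with no effect would appear at 86-88% if rescued within 1 to 2 hours, and a 5 v 5 test at the 0.05 level would flag it in about 5-11% of trials. At 8 hours it would appear at 75% and be flagged in about 79%. Section 7's close monitoring makes early rescue plausible, but the protocol gives no timing.

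The documents do not support saying that rescued time is expressly credited to the device, that the trial as a whole would hide a failing device, or that rescue would make the device look falsely selective. For the gradient, the expected effect is loss of contrast.

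**What to change.** In sections 2.2 and 6.3:

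1. Define the device endpoint as the share of monitored time in target without systemic cooling. In Group 2, time from the start of a rescue given for a missed target counts as not achieved by the device. Identify rescues given for deteriorating brain physiology and report them separately. State in advance whether the device can regain credit after a rescue ends, given the carry-over of cold saline.
2. Beside it, report the all-hours as-randomised comparison of in-target time and of the gradient, with rescue counts and durations for each patient.
3. Give the gradient on cervical cooling alone, for example up to first rescue, only as a supportive description labelled as subject to selection.
4. Record the start, stop and reason of each systemic cooling episode. The reason should distinguish rescue from induction, because section 3 reads as making saline induction common to both arms.

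The Synopsis and section 2 should also agree on whether these endpoints are primary or secondary.

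The cost is some wording and a small amount of extra bedside recording. The device's reported time in target may look less favourable. Rescue treatment itself is unchanged.

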# STUDY FLOW CHART

[figure not shown]

**Study Flow Chart.** Patient excluded due to immediate contraindications to cervical cooling will be counted. After randomization, patients will be treated and monitored up to 48 hours.

# STANDARD CLINICAL PROTOCOL

[figure not shown]

**Standard Clinical Protocol.** Patients are randomized to standard care or cervical cooling at STAGE 2 of the protocol (yellow box). Physiological data (including ICP, brain oxymetry and L/P metabolic profile) is captured in digital format as per standard practice on our unit.

## 1. BACKGROUND AND RATIONALE

Targeted temperature management is the standard of care for patients with acute neurological injuries, with level I evidence supporting its use following out of hospital cardiac arrest. The benefits of therapeutic hypothermia in brain injuries associated with trauma, haemorrhage or embolic events remains to be conclusively demonstrated.

It is undisputed that despite the neuroprotective effects of hypothermia, the induction and maintenance of systemic hypothermia is associated with side effects in clinical practice. A recent trial (Eurotherm3235) provides evidence against therapeutic hypothermia as an early measure to lower intracranial pressure [1]. Although the study provides no guidance on the use of therapeutic hypothermia for refractory intracranial hypertension, the findings of the Eurotherm trial raised concerns in regards to whether the risks of therapeutic hypothermia may outweigh its benefits even in patients with refractory intracranial hypertension. It is our opinion that therapeutic hypothermia should remain part of standard clinical protocols for patients with acute brain injuries and intracranial hypertension refractory to “level I” options [2].

Cervical temperature management may provide the benefits of hypothermic or normothermic neuroprotection without the renal, cardiac and infectious side effects of systemic hypothermia. This is a preliminary, **proof-of-concept investigation aiming to demonstrate that cervical cooling can safely induce selective brain cooling**. The study was instigated by the NIHR i4i panel, in consideration of a larger clinical trial of selective brain cooling following severe traumatic brain injury.

Our group previously conducted a preclinical study on large animals (sheep) with a neck cooling prototype, demonstrating that a differential reduction between the brain and body temperature could be induced by cooling the neck of the animal [3]. The prototype was also tested on healthy human subjects as part of the development process. In standard conditions (room temperature 23°C, supine resting position) we observed a reduction of tympanic temperature of 1°C, achieved over a period of one hour, followed by the onset of shivering. Testing the strategy in healthy subjects is clearly limited due to the lack of invasive brain temperature monitoring and for limited tolerance to hypothermia in non-sedated patients.

Patients who suffered severe traumatic brain injury are invasively monitored (including brain temperature, core temperature and haemodynamic and brain physiology parameters), they are sedated and they are treated with targeted temperature management as standard of care.

This preliminary study will assess the safety of the strategy of selective brain cooling, including whether the device is able to maintain brain temperature within the target

temperature range set by the treating physician, the type and frequency of side effects or complications associated with its use and its ability to induce and maintain a temperature differential between the brain and the body.

## 2. OBJECTIVES

### 2.1 Primary Objective

**Safety.** Describe number and severity of complications associated with induction and maintenance of hypothermia using selective cervical cooling:

- failure to maintain the brain within target temperature;
- number of instances where external cooling blankets or ice-cold saline had to be used as a rescue strategy to achieve target temperature;
- duration and severity of cerebral hyperthermia;
- any other adverse event;

### 2.2 Secondary Objectives

**Proof of concept.** Describe the ability of the device to deliver selective brain cooling, and its effectiveness:

- differential brain-to-core temperature as evidence of selective cooling (between-group comparison);
- brain temperature within target parameters (between-group comparison);

## 3. STUDY DESIGN

This is a preliminary, proof-of-concept, randomised, interventional study.

The study will enrol at least 10 patients admitted to the Neurosciences and Trauma Critical Care Unit (NCCU, Addenbrooke's) following severe traumatic brain injury requiring invasive brain temperature monitoring and target temperature management as standard of care.

Brain temperature monitoring includes: ICP, brain oxymetry, microdialysis, haemodynamic variables. Physiological parameters and blood tests are also sampled on the ICM+ platform and local electronic medical record systems.

Randomisation of at least 10 patients will be made after the treating clinician has set a target temperature of 35°C. Using predetermined identical envelopes, patients will be assigned to two groups:

**Group 1, Standard Care (5 patients):** Medical and surgical management as per local treatment protocol (Figure). **Targeted temperature management induced by rapid infusion of ice-cold saline and maintained by automated cooling blankets.**

**Group 2, Experimental Care (5 patients):** Patients allocated to group 2 will receive the same treatment as those in group 1, with the exception of maintenance of **target temperature by using selective cervical cooling.**

Cervical cooling will be delivered with a purpose built prototype developed by Neuronguard. Brain temperature, core temperature (bladder or oesophageal), ICP and other physiological parameters will be continuously monitored and captured digitally as per standard local practice. Temperature targets are determined by the treating clinician, they will be recorded by a chart at the bedside, updated hourly, with brain temperature targets expressed as absolute values  $\pm 0.5^{\circ}\text{C}$ . Monitoring will continue for 48 hours, irrespective of temperature targets (i.e. to include rewarming, if indicated).

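### The protocol contradicts itself on how Group 2 is induced, so the saline part of the primary rescue count depends on the reading; systemic cooling started for brain physiology alone is not counted as rescue

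*Protocol*

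**What the plan says.** Section 3 describes Group 1 in two phases: "Targeted temperature management induced by rapid infusion of ice-cold saline and maintained by automated cooling blankets". It then says that Group 2 patients "will receive the same treatment as those in group 1, with the exception of maintenance of" "target temperature by using selective cervical cooling".

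Section 2.1 sets the primary (safety) objective: "Describe number and severity of complications associated with induction and maintenance of hypothermia using selective cervical cooling". One of its four listed components is the "number of instances where external cooling blankets or ice-cold saline had to be used as a rescue strategy to achieve target temperature". The primary objective in the synopsis also names induction and lists the same rescue component.

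The synopsis describes the experimental arm as cervical cooling, with systemic cooling permitted as rescue when targets are missed. Its Study Design row presents systemic and cervical cooling as alternatives.

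Section 7 says the treating clinician will turn to systemic cooling, by ice-cold saline or surface cooling, in Group 2 patients when the target cannot be reached "or if there is any deterioration in brain physiology".

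**The concern.** Two things do not fit together.

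The first is the experimental treatment itself. Section 3 reads as saline induction followed by device maintenance. The objective and the synopsis read as the device doing both, with saline held back for rescue. A first-in-human study whose primary aim is to describe the safety of a device must be clear about which phases the device delivers. If saline induces, complications arising during induction would be reported as belonging to cervical cooling. Early brain-to-core readings, which serve the secondary objective, would also carry the effect of a systemic infusion.

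The second is the rescue count. It is the primary component that shows how often the device had to be supplemented. Its saline part cannot be scored until the first question is settled. Its definition also names one trigger, where Section 7 names two.

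The results are meant to inform a decision on a larger trial, so under-reported or wrongly attributed use of systemic cooling would carry forward.

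**Working it through.** The protocol states no power, alpha or effect size, and Section 6.1 says no formal sample size calculation was indicated. There is no planned figure to reproduce. The check is a comparison of texts, followed by simple counting.

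**Step 1. What induces hypothermia in Group 2?**

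| Place in protocol | Role of ice-cold saline or systemic cooling in Group 2 |
|---|---|
| Section 3 | Group 1 is "induced by rapid infusion of ice-cold saline and maintained by automated cooling blankets"; only maintenance is changed for Group 2, so saline induction carries over |
| Synopsis, Study Design | Systemic or cervical cooling, as alternatives |
| Synopsis, experimental arm | Systemic cooling as rescue |
| Synopsis and Section 2.1, primary objective | Induction attributed to cervical cooling; saline and blankets counted as rescue |
| Section 7 | Saline or surface cooling as a fallback |

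Section 3 distinguishes induction from maintenance in the Group 1 description, immediately before it exempts only maintenance for Group 2. The plain reading is therefore saline induction in both arms. The other passages point the other way.

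**Step 2. Consequence of each reading.**

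- *Reading A, saline induces.* The opening infusion is assigned treatment and is not rescue. The objective's reference to "complications associated with induction and maintenance of hypothermia using selective cervical cooling" then covers a phase the device does not deliver. A further infusion before target is first reached could be called continued induction or rescue. The text shown gives no time point, first attainment of target or device start to decide between them.
- *Reading B, the device induces.* Any saline is rescue and is counted. Section 3 is then wrong as written.

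**Step 3. Size.** Group 2 has 5 patients (Section 3). Assume one opening infusion in each; the protocol does not give this number. The contribution to the rescue count is:

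- Reading A: 5 × 0 = 0 instances.
- Reading B: 5 × 1 = 5 instances.

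So the reading alone can move the saline part by up to 5 under that assumption. Blanket use does not move: Section 3 replaces blankets with the device for maintenance in Group 2, so blankets are rescue under A and B alike.

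**Step 4. Triggers.** Section 7 gives two reasons for systemic cooling in Group 2. Set against the definition in Section 2.1:

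| Reason for systemic cooling | In the rescue count? |
|---|---|
| Target not achieved | Yes |
| Target not achieved and brain physiology deteriorating | Yes |
| Brain physiology deteriorating, target achieved | No |

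The third row is a move to systemic cooling that Section 7 permits and the primary count omits. The protocol gives no expected frequency, so its size cannot be stated.

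**The case against.** The strongest reply is that the word rescue already settles the count. Saline given as assigned induction is not rescue in ordinary language, so a workable count exists under either reading. That is largely right. A reader might infer that the count starts at 5 of 5 before the device has failed anyone, because the same infusion is both assigned treatment and a counted event. The text does not support this: reaching it means dropping the qualifier in Section 2.1, and under no single reading is one infusion both. What remains is that the protocol does not say which reading applies, and under Reading A nothing shown separates late induction saline from early rescue saline.

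A second reply is that the flow chart and the standard clinical protocol figure are not shown and may set out the cooling steps. This stands as a limit on the claim that nothing separates the two uses. A figure that did so would still leave Sections 2.1 and 3 in conflict.

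A third is that episodes triggered by physiology are not lost. The primary objective has a catch-all for other adverse events, Section 5.1 lists uncontrollable intracranial hypertension as serious, and physiology is recorded continuously. This is fair: the underlying events may well be reported, but not as use of systemic cooling. A count restricted to missed temperature targets is a coherent measure of cooling performance, but it is not a full count of supplementation in the device arm.

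Finally, this is a small descriptive pilot, and no power calculation rests on the count. That limits the damage. It does not remove a contradiction about what the experimental arm receives.

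**Conclusion.** The concern holds as a contradiction in the protocol, not as missing detail. Section 3 implies saline induction in Group 2; the primary objective attributes induction to the device; and the synopsis and Sections 2.1 and 7 treat systemic cooling or saline there as rescue. One of four primary components is affected, and only in its saline part. The range of 0 to 5 instances in 5 patients rests on the assumption of one opening infusion per patient. Separately, systemic cooling started only for deteriorating brain physiology falls outside the rescue count, so crossover to systemic cooling would be under-reported by an unknown number of episodes.

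Three stronger conclusions are tempting and are not supported:

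- That the whole rescue count is uninterpretable. Blanket use is clear under either reading, and the saline part can be repaired.
- That the omitted episodes are the more serious ones. No section ranks the triggers by severity.
- That centres would report opposite results. The trial runs in a single unit; the risk is of different scoring by assessors within it.

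**What to change.** 1. Reconcile the synopsis (Study Design, experimental arm, primary objective) and Sections 2.1, 3 and 7 on how hypothermia is induced in Group 2. Which method is used is for the clinical team to decide.
2. Word the primary objective so that it claims complications only for the phase or phases the device delivers.
3. Define the rescue count as every systemic-cooling episode in Group 2 that is not part of assigned induction. State where assigned induction ends, if there is one.
4. Report the count by trigger: target temperature not achieved, or deterioration in brain physiology. The temperature-only count stays available as a subset.

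The cost is amendment wording and one trigger field on the data form. The reported rescue count may be higher than under the present definition, because episodes triggered by physiology alone would now be included.
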